## Introduction

The availability of anti-retroviral therapy (ART) has improved the life expectancy of persons living with HIV worldwide (1). However, a major concern is that, HIV morbidity and mortality have improved drastically among adults, which is not the case among young people (2). Research has shown that young people tend to experience worse immunological and viral suppression outcomes compared to adults (3–6), which in turn contributes to their higher morbidity and mortality (7).

Barriers to successful care of youth with HIV include mental health disorders, poor medication adherence, socioeconomic instability, and HIV-related stigma (8). Also transition of care from pediatric to adult clinics has been described as a challenging period in which the young people have to deal with anxieties, excessive anger, and lack of social support, self-esteem and self-efficacy (9). Consequently, they are prone to poor linkage to care, attrition from care and treatment (10).

In Uganda, the national HIV treatment guidelines include psychosocial support services in the HIV care package (11). However, the nature of psychosocial support is not structured and may not target common psychosocial challenges such as stigma, depression or post-traumatic stress. Enhanced or Intensive adherence counseling has long been used to mitigate non-viral suppression; however, recent findings from Ugandan studies indicate that this strategy may not be sufficient (12, 13).

A retrospective cohort study on all children aged 9 months to 19 years that had been enrolled into 15 HIV care programs in 15 districts supported by the Infectious Diseases Institute (IDI) assessed the outcome of Intensive adherence counseling among 449 children with viral non-suppression (13). A repeat viral load test performed on 274 children who had completed three IAC sessions indicated that 212/274 (77%) were unsuppressed and 62 (23%) were suppressed. There was no report of any other specific psycho-social intervention provided to children with viral non-suppression in the above mentioned 15 HIV care programs.

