**IAC Session 3**	
Assess	Do as in IAC Session 2
Advise	Do as in IAC Session 1
Assist	Do as in IAC Session 1
Agree on	Do as in IAC Session 1
Arrange	Review Adherence Scores For 1st, 2nd And Current IAC Visits • If Adherence Score Is Consistently Good (>95%) For Three Consecutive IAC Visits, Give 1 month Appointment For 2nd VL Bleeding • If Adherence Score Is Not Consistently Good For Three Consecutive IAC Sessions, Give Appointment For 4th IAC Session Give Appointment For 2nd Bleeding For VL Test (After 1 Month) • Remind And Emphasize To Client To Keep The Next Appointment. • Flag The Client's File As Due For Repeat VL Testing (Indicate Due Date On The Red Sticker) Discuss Reminder Plans With Clients Who Are Due For Bleeding • Provide ARV Drugs For 1 Month (Strictly) • Call Client 1 Week To The Due Date To Remind Them Of Appointment

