#### Participant safety

During baseline assessments, participants will be carefully screened and individuals for whom the interventions are deemed medically inappropriate or unsafe will be excluded as described in the exclusion criteria. Independent outcome assessors will screen all participants for adverse events at the end of treatment and at 6 months after the end of the intervention using a standard interview and reporting form.

Any unfavorable and unintended sign or symptom associated with the participation in group support psychotherapy, regardless of whether it is considered related to the therapy will be regarded as an adverse event (AE).Any AE that results in any of the following outcomes: Death, Life-threatening, Event requiring inpatient hospitalization, Persistent or significant disability/incapacity will be regarded as a serious adverse event (SAE). Expected AEs associated with this study would be suicide attempts due to lack of treatment response to the group support psychotherapy.

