**Primary outcomes**					
Indicators of feasibility	The proportion of eligible participants who take up either intervention (**Reach**) The proportion who attended all 8 sessions of either intervention (**Dose delivered**) The proportion who are lost to follow-up (**Attrition**) will be determined from the attendance registers		✓		
Indicators of acceptability	A 9-item questionnaire (34) will assess participant's satisfaction, the group facilitators’ knowledge and attitudes, and the participant evaluation of the intervention's ability to reduce stress		✓		
Adherence to ART	One question “During the past three weeks, on how many days have you missed taking all your medication doses?”	✓		✓	✓
Viral Load	Medical charts of study participants	✓		✓	✓

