#### Quantitative data

For the quantitative data, we will do bivariate analyses with *χ*^2^ tests and independent two-sample *ttests* to compare categorical and continuous baseline demographic and psychosocial variables between study groups respectively. Similarly, we will also do bivariate analyses to compare these variables between those who had completed all sessions (completers) and those who had not (non-completers). Although randomisation to GSP and GHE will be done at the individual level, study participants will receive their respective interventions in groups (clusters). Since individuals within a cluster are likely to be correlated, we will use cluster-level analyses to make allowance for intra-cluster correlation.

We will apply ttests to cluster-level summaries, which is a robust method of analysis for cluster data (46). Specifically, we will use the STATA collapse command to obtain cluster-level summaries of the study outcomes from data on individual participants. This procedure will reduce the data from 120 individual participants to 12 groups. We will then use the *clttest* command to compare cluster means across treatment groups.

To do an intention-to-treat analysis, we will impute missing values with several imputations. We will construct five imputed datasets with the multivariate normal model assuming that data were missing at random. The participants complete baseline data will be used to create the multiple imputation datasets.

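### One missing-at-random rule covers every missing viral load, so participants who died or left HIV care can be imputed as suppressed

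*Protocol article*

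**What the plan says.** The Quantitative data section gives one rule for missing outcomes: "To do an intention-to-treat analysis, we will impute missing values with several imputations". The method follows: "We will construct five imputed datasets with the multivariate normal model assuming that data were missing at random". The input is then named: "The participants complete baseline data will be used to create the multiple imputation datasets". No outcome and no reason for missingness is exempted.

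Table 2 lists viral load as a primary outcome at 0, 6 and 12 months and gives its source as "Medical charts of study participants". No study blood draw is described. The eligibility section requires at least 1,000 copies/ml at entry, so every participant starts unsuppressed.

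Death and loss are both foreseen. Participant safety defines serious events to include "Death, Life-threatening, Event requiring inpatient hospitalization". Table 2 makes attrition a primary feasibility indicator that "will be determined from the attendance registers". The Introduction describes this age group as prone to dropping out of care and treatment. No expected attrition rate is given.

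**The concern.** A chart viral load needs someone who is alive, attends a clinic and is bled. A participant who dies before the reading cannot have one, and one who has left HIV care probably does not. For both, the gap is related to the outcome. Imputation from baseline data cannot see that either event occurred, so it gives these people the results of similar participants who stayed. For someone who has died, an imputed suppressed viral load has no meaning.

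The results have several uses. Sample size justification says the pilot supplies parameters for sizing the definitive trial, so an inflated control-arm suppression rate would pass into that calculation. Cost-effectiveness analysis intends viral load as its outcome. Ethical considerations ties participants' access to the intervention to its apparent benefit, including on suppression.

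**Working it through.** **Inputs from the article.** 60 per arm (Sample size justification). In the cohort cited in the Introduction, 449 unsuppressed children received intensive adherence counselling (IAC), and "A repeat viral load test performed on 274 children who had completed three IAC sessions indicated that 212/274 (77%) were unsuppressed"; the other 62 were suppressed.

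**Assumptions.** The trial's missing fraction *d*, and any suppression rate with group support psychotherapy (GSP), are not in the article. The cohort's rate among those tested stands in for the rate among observed participants, *p*.

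**Step 1: reproduce the cited figures.** 212/274 = 77.4% and 62/274 = 22.6%, matching the stated 77% and 23%. Children with no reported repeat test: 449 − 274 = 175, and 175/449 = 39.0%.

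**Step 2: effect on the level in one arm.** Under missing at random the expected result is *p* whatever *d* is. If all missing are unsuppressed, it is *p*(1 − *d*). The expected number of missing people counted as suppressed is 60 × *d* × *p*. With *p* = 22.6%:

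| Missing | Planned imputation | All missing unsuppressed | Gap (points) | Missing people counted as suppressed, of 60 |
|---|---|---|---|---|
| 10% | 22.6% | 20.4% | 2.3 | 1.4 |
| 20% | 22.6% | 18.1% | 4.5 | 2.7 |
| 39% | 22.6% | 13.8% | 8.8 | 5.3 |

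The last row equals 62/449 = 13.8%.

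**Step 3: does the normal model produce suppressed values?** In a simulation (2,000 runs, 60 per arm, five imputations of log10 viral load from baseline viral load, with and without arm in the model, assumed viral load distributions), about 26% of missing participants were imputed below 1,000 copies/ml when 22.6% of observed participants were suppressed. Everyone starting at or above 1,000 does not prevent this.

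**Step 4: effect on the difference, GSP minus IAC, if all missing are unsuppressed.**

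- *Equal loss, no effect.* Both rules give 0 points. Only the level is wrong.
- *Equal loss of 20%, observed rates 22.6% (IAC) and an assumed 45% (GSP).* Imputation gives 45 − 22.6 = 22.4 points; the alternative gives 0.80 × 22.4 = 17.9.
- *GSP loses more: 10% (IAC) and 30% (GSP) missing, 22.6% observed in both.* Imputation gives 0. The alternative gives 0.70 × 22.6 − 0.90 × 22.6 = 15.8 − 20.4 = −4.5 points (unrounded inputs). Imputation flatters GSP.
- *IAC loses more: 39% and an assumed 20% missing, 13.8% of all randomised suppressed in both arms.* Imputing at each arm's own observed rate gives 13.8/0.61 = 22.6% for IAC and 13.8/0.80 = 17.3% for GSP, a false deficit of 5.4 points for GSP (unrounded). Imputing at the pooled observed rate, 27.6/1.41 = 19.6%, gives 13.8 + 0.39 × 19.6 = 21.4% and 13.8 + 0.20 × 19.6 = 17.7%, a deficit of 3.7 points.

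The sign therefore follows from which arm loses more, and the size also depends on whether arm is in the imputation model, which the article does not say.

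**The case against.** **The reasons for missing results are unknown.** Transfers, incomplete charts and tests outside the window would also leave gaps, and missing at random may be reasonable for those. This stands. It is why the point is limited to death and documented loss to care, and why counting every missing result as failure should not be the main rule: it would penalise an arm for administrative gaps.

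**Stopping counselling is not the same as having no viral load.** A reader might infer that it is, because the IAC guide books the repeat test at the third session: "If Adherence Score Is Consistently Good (>95%) For Three Consecutive IAC Visits, Give 1 month Appointment For 2nd VL Bleeding". That guide describes one routine repeat test. It does not govern the trial's 6- and 12-month chart readings, and someone who stops counselling but still collects refills may have a value. The documents do not support that inference.

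**The 39% is not a forecast.** The Introduction does not say why 175 children have no reported repeat test, and the cohort is a retrospective programme series aged 9 months to 19 years. The trial has research staff in the clinics, reimburses transport and plans home visits. Loss could be much lower; at 5 to 10% missing the level shifts by only about 1 to 2 points.

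**The bias does not necessarily run against GSP.** A reader might infer that it does, because Retention describes home visits for missed group sessions and nothing equivalent for missed counselling. That makes unequal loss plausible but does not establish it.

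**The pilot is imprecise anyway.** At 22.6% and 17.3% with 60 per arm, the simple standard error of the difference is √(0.226 × 0.774/60 + 0.173 × 0.827/60) = 7.3 points, ignoring clustering. That is larger than the 5.4-point illustration. True, but a systematic error in the level still passes into the design of the definitive trial.

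**Missing at random is conditional on the model, and an analysis plan may add sensitivity analyses.** Both are fair. But the article names baseline data only, further covariates would not give meaning to a viral load after death, and added sensitivity analyses would leave the stated main rule in place.

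**Conclusion.** The point holds in a limited form. As written, the plan can assign a suppressed viral load to a participant who died or left HIV care before the reading. That these participants have no chart value is certain for a death before the visit and an inference, though a likely one, for loss to care.

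The overstatement of suppression is real to the extent that those lost to care are unsuppressed. At 22.6% among those observed it would be about 2 points at 10% missing and 4.5 points at 20%, if all missing are unsuppressed. The 8.8 points at 39% illustrates how large it could become, not what to expect. The arm difference is affected when loss differs between arms or when there is a real effect, and its direction cannot be stated in advance. The 5.4- and 3.7-point figures are constructed examples and should not be quoted as estimates of bias in this trial.

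**What to change.** For viral suppression at 6 and 12 months:

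1. Count participants who died, or who are documented as out of HIV care at the visit, as not suppressed.
2. Use multiple imputation only for those alive and in care, or with an administrative gap such as a transfer or incomplete chart.
3. Report two sensitivity analyses: all missing counted as not suppressed, and the planned missing-at-random imputation for everyone.
4. Tabulate missing viral loads by arm and reason.

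Trial status reports that analysis is in progress, so the change should be dated, with a statement of whether outcome results by arm had been seen.

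The cost is a few sentences of analysis wording and one extra tabulation of vital and care status, from charts already being read. Suppression rates will look slightly lower, and some people treated elsewhere may be misclassified as out of care; the two sensitivity analyses show how much that matters.

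### The imputation plan names baseline data as its source and mentions neither arm, therapy group nor follow-up outcomes; if arm is left out, the effect shrinks by about the missing fraction

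*Protocol article*

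**What the plan says.** The protocol article does not leave missing data to a later document. Under Quantitative data it ties imputation to the main analysis: "To do an intention-to-treat analysis, we will impute missing values with several imputations". It fixes the number of datasets, the model and the assumption: "We will construct five imputed datasets with the multivariate normal model assuming that data were missing at random". It then names the source: "The participants complete baseline data will be used to create the multiple imputation datasets". No other section adds arm, therapy group or follow-up measurements to the imputation.

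The same section recognises clustering in the analysis ("Since individuals within a cluster are likely to be correlated, we will use cluster-level analyses to make allowance for intra-cluster correlation") and compares cluster means by t test: "This procedure will reduce the data from 120 individual participants to 12 groups".

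Table 2 gives the outcomes concerned. Adherence is a single question, "During the past three weeks, on how many days have you missed taking all your medication doses", so the answer is a count from 0 to 21. Viral load comes from "Medical charts of study participants". Both are due at baseline and at 6 and 12 months. The psychosocial scales are also measured at 2 months.

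**The concern.** An imputation model should contain everything the analysis model contains. The analysis compares arms through therapy-group means, yet the only input named for the imputation is baseline data. Three consequences follow if the sentence is applied as written.

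- Without arm, missing values in both arms are drawn from one common distribution, which pulls the arm difference toward zero.
- Without the other follow-up visits, information about a missing 6- or 12-month value is discarded. That information would also make missing at random more plausible.
- Without therapy group, imputed values carry no group effect, so variation between group means is understated.

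The Sample size justification section says that the pilot is there to supply parameter estimates for the main trial's sample size. A diluted effect would therefore not stay in this report.

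**Working it through.** **Inputs from the article.** Five imputations, multivariate normal, missing at random, 120 participants in 12 groups (Quantitative data); 60 per arm (Sample size justification); 62/274 = 23% suppressed after counselling in the cited cohort (Introduction).

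**Assumed, because the article gives no figure.** Missing 10%, 20% or 30%, completely at random and equal in both arms; ICC 0.05 to 0.20; six groups per arm; 45% suppression with GSP; mean missed days 4 (control) and 2 (GSP), overdispersed and capped at 21.

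**1. The plan's own figures.** Five datasets is a choice with no derivation to reproduce. The cluster count is coherent: 120/12 = 10 per group.

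**2. Why omitting arm dilutes the effect.** Let Δ be the true difference and f the fraction missing in each arm. With arm omitted and baseline balanced, imputed values have the same expectation in both arms, so

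estimate ≈ (1 − f)Δ + f × 0 = (1 − f)Δ.

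This gives 0.90Δ, 0.80Δ and 0.70Δ at f = 0.10, 0.20 and 0.30.

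**3. Simulation.** 1,500 trials per setting, 12 groups of 10, ICC 0.05, five normal-model imputations from one baseline covariate, difference in cluster means:

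| Outcome | Missing | Full data | Arm omitted | Ratio | Ratio, arm included |
|---|---|---|---|---|---|
| Suppression | 10% | 0.220 | 0.200 | 0.906 | 1.001 |
| Suppression | 20% | 0.221 | 0.176 | 0.799 | 0.999 |
| Suppression | 30% | 0.222 | 0.157 | 0.707 | 1.003 |
| Missed days | 10% | −1.960 | −1.757 | 0.896 | 0.996 |
| Missed days | 20% | −1.938 | −1.559 | 0.804 | 1.005 |
| Missed days | 30% | −1.910 | −1.338 | 0.700 | 1.005 |

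A 22-point difference in suppression becomes about 20, 18 and 16 points.

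For a continuous outcome with a 0.5 SD effect, baseline correlation 0.4 and ICC 0.05, the estimate averages 0.44, 0.40 and 0.35. At 20% missing the chance of detecting it falls from about 55% to about 33%.

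**4. Carry-over to the main trial.** Sample size varies as 1/Δ². If the pilot estimate were used directly, the required number would be multiplied by 1/0.90² = 1.23, 1/0.80² = 1.56 or 1/0.70² = 2.04.

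**5. Arm included, therapy group omitted (20% missing).**

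| ICC | Mean reported SE | Actual SD of estimate | Ratio |
|---|---|---|---|
| 0.10 | 0.246 | 0.265 | 0.93 (7% too small) |
| 0.20 | 0.281 | 0.317 | 0.89 (11% too small) |

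At ICC 0.20 the type I error is 7.3%, and 8.1% at 30% missing, against a nominal 5%. At ICC 0.05 and 20% missing the effect is negligible. When arm is omitted as well, dilution dominates and the standard error is not understated.

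**6. Normal model.** About 22% of imputed missed-days values fall outside 0 to 21, nearly all negative. If suppression were imputed as a 0/1 variable, about 33% of draws would fall outside that range. With arm in the model, neither biased the mean difference (last column in step 3).

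**7. Five imputations.** Relative efficiency is 1/(1 + FMI/m), where FMI is the fraction of missing information.
- FMI 0.2: 1/1.04 = 0.962 with m = 5, and 1/1.01 = 0.990 with m = 20.
- FMI 0.3: 0.943 and 0.985.
- Standard-error inflation with m = 5 is √(1 + FMI/5), or 1.01 to 1.03 for FMI 0.1 to 0.3.

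**The case against.** The strongest reply is that the text is ambiguous rather than wrong. It says that baseline data will be used, not that nothing else will be. A multivariate normal model is a joint model, so follow-up outcomes imputed together would inform one another. The full list of imputation variables commonly sits in an analysis plan that is not shown. This stands in part. The shrinkage cannot be stated as a fact about the trial. But the article goes beyond silence: it fixes the method and names one source, and an analyst who follows that sentence would leave arm out.

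A reader might infer several stronger criticisms that the article does not support:

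- **Impossible suppression values.** Table 2 lists viral load, and nothing says that suppression is imputed as 0/1. Imputing log viral load and then applying the cut-off gives only valid values.
- **Implausible draws as bias.** The analysis compares cluster means, and out-of-range draws did not distort these once arm was included.
- **Five imputations as a serious defect.** The cost is 1% to 3% in the standard error.
- **A missing chart value means the young person has left care.** The Introduction mentions attrition from care in young people, but no section links it to missing charts. Missing at random is a conventional primary assumption.

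The objection also limits the remedy. GSP groups are sex- and age-specific (Interventions), so group largely determines sex and age band, and entering all three is collinear. Logistic imputation by arm, with group, five clinics (Limitations) and all visits on about 60 participants, risks perfect prediction. With six groups of 10, 20% missing (8 observed per group) and independence, the chance that at least one group has no suppressed member is 1 − (1 − 0.77⁸)⁶ = 55% at 23% suppression, and 1 − (1 − 0.60⁸)⁶ = 10% at 40%.

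**Conclusion.** The point holds conditionally. The article fixes an imputation method whose only named source is baseline data. Applied literally without arm, it reduces the estimated effect to about 0.90, 0.80 and 0.70 of its size at an assumed 10%, 20% and 30% missing, and it does not use the other follow-up visits. Including arm removes the dilution. If arm is included but therapy group is not, a smaller problem remains: a standard error about 7% to 11% too small at ICCs of 0.10 to 0.20, on an assumed 20% missing. The poor fit of a normal model to the missed-days count is a secondary matter, and the number of imputations is minor. The dilution is close to the missing fraction under equal, random missingness with balanced baseline. The rates and ICCs are assumptions, because the article states neither. The clarification should be made, since the estimates are meant to inform a definitive trial.

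**What to change.** Amend the imputation paragraph as follows:

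1. Impute separately by arm, or with arm in the model, using baseline data plus all follow-up outcome measurements.
2. Allow for therapy group where it can be estimated, for example with a random or cluster-mean term, without also entering the collinear sex and age band.
3. Impute log viral load and derive suppression at 1,000 copies/ml, the threshold in the eligibility criteria. Use predictive mean matching for missed days.
4. Use about 20 or more imputations. This is a minor gain at almost no cost.
5. Add one sensitivity analysis that counts missing viral load as not suppressed in both arms.

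The cost is slightly more analysis work. Trial status reports that recruitment has closed and that analysis of baseline, 6- and 12-month data is in progress. The change would therefore be made with data in hand, so it must be dated, justified and reported as such.
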